### Recruitment of controls

Healthy participants (*n* = 100 from Guatemala and *n* = 150 from India) who have not had a febrile episode in the last three months are enrolled as HCs to the cohort, which will further be age- and sex- matched. Samples from these participants are tested for anti-dengue IgM and NS1 ELISA to rule out ongoing asymptomatic dengue infection, and anti-dengue IgG ELISA to check for past dengue infection. Each of the control participants is also asked to provide a detailed medical history.

### Study procedures

A single blood sample is collected from the non-hospitalized patients, while two blood samples per participant are collected from the hospitalized patients. The first one is taken within the first two days of hospitalization, and the second at discharge. A questionnaire is administered at the time of blood collection (Table 2). Total participation time is less than 15 min. For Guatemala, whole blood is collected in Tempus™ tube for transcriptomics and in Cytodelics medium for flow cytometry, while plasma from EDTA blood and serum are collected for proteomics, metabolomics and glycomics. For India, whole blood (3 ml) is collected in Tempus™ tubes for transcriptomics and 7–8 ml in BD Vacutainer CPT™ Cell Preparation Tubes for plasma separation and PBMC isolation.

**Table 2 Tab2:** Routine clinical investigations performed in dengue cases in all the cohorts

Parameters	Unit of Measurement
Age	In years
Sex	Male/Female

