### Study design

COMBAT is a prospective, multicenter, observational longitudinal study designed to characterize host responses to dengue infection without altering standard clinical management.

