• Patients below the age of 18 years • Pregnant, immunocompromised or undergoing chemotherapy, on steroids or immunosuppressive drugs in the last year or with liver cirrhosis • Co-infection with a non-dengue pathogen • Cases with a lab-confirmed dengue infection within the past three months

The study is designed to investigate the progression of dengue infection in patients, from without warning signs, to with warning signs to severe dengue, which varies between cases. If a patient recruited in the category “DwoWS” develops symptoms correlating with severity and receives intensive care, they will then be re-categorized into the second “DWS” or third “SD” group. Keeping in mind the complexity of dengue presentation, subcategorization of the patients will be performed as necessary to establish the degree of severity depending on the timepoint of recruitment and the points of sample collection. The highest (peak) severity category reached during the acute illness constitutes the participant’s definitive severity classification and serves as the primary outcome label for all biomarker analyses. For incorporation into the biomarker discovery and validation analyses, the earliest sample for each participant collected before or at the point of clinical deterioration is used as the predictor, and the definitive peak severity category is used as the outcome.

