**Disease symptoms at the time of sampling**	
Duration of symptoms onset at sample collection	In days
Duration of hospitalization at sample collection	In days
Fever	Yes/No
Body pain	Yes/No
Joint pain (arthralgia)	Yes/No
Rash	Yes/No
Nausea/vomiting	Yes/No
Night sweats	Yes/No
Retro-orbital pain	Yes/No
Abdominal pain	Yes/No
Headache	Yes/No
Chills/ rigor	Yes/No
Burning micturition	Yes/No
Dizziness	Yes/No

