Multi-omics approaches, including proteomics, metabolomics, transcriptomics, and immune profiling, have expanded biomarker discovery by capturing integrated signatures of immune activation, metabolic rewiring, endothelial injury, and organ dysfunction [23]. In chronic and noncommunicable diseases, large-scale plasma proteomic studies have successfully identified both shared and disease-specific molecular signatures with predictive value. However, applying similar frameworks to acute viral infections is more complex because host molecular profiles change rapidly with viral kinetics, symptom onset, immune activation, treatment, and recovery. Longitudinal COVID-19 and dengue studies, show that disease severity is associated not only with specific molecular markers but also with their temporal trajectories, highlighting the importance of sampling time and disease phase [24, 25].

In dengue virus (DENV) infection, multi-omics approaches have substantially advanced our understanding of the molecular signatures linked to severe clinical outcomes, including plasma leakage, hemorrhage, and shock [26]. Transcriptomic and proteomic studies have identified early dysregulation of interferon signalling, complement activation, and platelet degranulation pathways as markers of disease severity [27–29]. In parallel, metabolomic and lipidomic analyses have revealed alterations in metabolic processes, e.g., in phospholipid metabolism, arachidonic acid signalling, and amino acid utilization, reflecting immune activation, vascular dysfunction, and endothelial injury [30, 31]. Integrative multi-omics studies further suggest that metabolic and proteomic changes may emerge before overt clinical deterioration, supporting their potential as early prognostic indicators. However, variability in sampling time, host genetic background, immune history, and co-circulating DENV serotypes continues to limit cross-study reproducibility. These challenges highlight the need for temporally harmonized, geographically stratified, and serotype-aware cohorts to enable robust biomarker validation.

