Several limitations warrant consideration. As an observational study, COMBAT cannot establish causal relationships between identified molecular signatures and clinical outcomes. Differences in timing of sample collection relative to symptom onset may influence observed molecular profiles. In addition, variability in transmission patterns and diagnostic capacity across sites may affect recruitment rates and cohort composition. Although laboratory-based inclusion criteria strengthen internal validity, they may reduce the ability to capture the full clinical spectrum of dengue-like illness during low-transmission periods. Achieving an appropriate balance between methodological rigor and epidemiological representativeness remains a central challenge in cohort-based infectious disease research. Finally, although we aim to develop a unified biomarker panel applicable across both settings, differences in host genetic background, environmental exposures, and other population-specific factors may limit the identification of a fully overlapping biomarker signature. In such cases, we will develop and validate region-specific biomarker panels while also identifying conserved biological pathways that may support broader cross-population applicability.

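### The first inpatient sample can follow up to two days of care and still serve as the predictor, so severity signatures can partly reflect treatment already given

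*Protocol article*

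**What the plan says.** Study procedures sets the sampling scheme: "A single blood sample is collected from the non-hospitalized patients, while two blood samples per participant are collected from the hospitalized patients". For inpatients, "The first one is taken within the first two days of hospitalization, and the second at discharge". The window is tied neither to the moment of admission nor to the start of treatment. (The Abstract can be read as two samples during the stay plus one at discharge. That needs reconciling but does not affect this point.)

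Study cohorts, in the text after Table 1, defines predictor and outcome: "the earliest sample for each participant collected before or at the point of clinical deterioration is used as the predictor", and "The highest (peak) severity category reached during the acute illness constitutes the participant’s definitive severity classification". Study design describes the study as "designed to characterize host responses to dengue infection without altering standard clinical management", so usual care runs its course before the draw.

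The Discussion states that "host molecular profiles change rapidly with viral kinetics, symptom onset, immune activation, treatment, and recovery". Table 2 includes "Duration of hospitalization at sample collection", in days, but no entry for fluids, blood products or drugs received. The limitations paragraph mentions timing only with respect to illness onset: "Differences in timing of sample collection relative to symptom onset may influence observed molecular profiles".

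**The concern.** The predictor rule looks to deterioration and is silent on treatment. A patient admitted, treated from the first hours, sampled on day two and worsening on day three meets the rule in full. An outpatient on the same day of illness is sampled with no inpatient care. If care before the draw is more common or more intense in patients who reach a higher peak severity, which is plausible, treatment is associated with the outcome label and, on the article's own account, with the molecular profile. That is confounding of the severity contrast, and matching or adjusting for day of illness does not remove it.

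At stake is the intended use. A primary endpoint is a panel that predicts progression to severe dengue, and the Discussion presents it as a tool for early triage. A marker that partly records that a patient has already been treated would look prognostic in these data and do less well at the point of triage.

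**Working it through.** **The plan's own figure.** The only computed number in the article is 67 subjects per group for RNA-seq (Statistical analysis). It reproduces approximately. Per-gene alpha = 80 × 0.01 / (19,900 × 0.99) = 4.06e-5. Then n = (z₁₋α/₂ + z₀.₈)² × [(1/5 + 0.5) + (1/10 + 0.5)] / (ln 2)² = 66.2, rounded up to 67. It has no bearing on this point.

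**Does the text allow treated predictor samples?**
1. The inpatient draw may fall anywhere in a two-day window (Study procedures).
2. Care is not altered or held back for the study (Study design).
3. Eligibility as predictor depends on deterioration only (Study cohorts). The rule excludes samples taken after deterioration; it does not exclude samples taken after supportive care has begun.
4. Table 2 as printed would show days in hospital at the draw, but not what was given.

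So yes. How often this happens is not stated: the article gives no share hospitalized per group, no treatments and no actual sampling delays.

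**How much could it matter?** Both inputs below are assumptions. Let treatment shift an analyte by d SD, let the treated share of predictor samples differ by q between two severity groups, and let severity have no true effect. The apparent group difference is d × q SD, its expected z is d × q × √(n/2), and the chance of passing two-sided p<0.001 is about Φ(d × q × √(n/2) − 3.29). Example: n = 100, d = 0.8, q = 0.5 gives 0.4 × 7.07 = 2.83, and Φ(−0.46) = 32%.

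| n per group | d (SD) | q = 0.25 | q = 0.50 | q = 0.75 | q = 1 |
|---|---|---|---|---|---|
| 100 | 0.5 | 0.8% | 6% | 26% | 60% |
| 100 | 0.8 | 3% | 32% | 83% | 99% |
| 100 | 1.0 | 6% | 60% | 98% | ~100% |
| 150 | 0.8 | 6% | 57% | 97% | ~100% |

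At a threshold of 0.01/1034, with n = 100 and d = 0.8, the four values fall to 0.1%, 5.5%, 43% and 89%. Larger groups make the false signal easier to detect; they do not shrink the bias.

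**One concrete mechanism.** Assume plasma volume expands by 10% to 20% in treated patients and the between-patient SD is 0.5 log2 units. Analytes fall by log2(1.1) = 0.14 to log2(1.2) = 0.26, that is 0.28 to 0.53 SD. The standard error is 0.5 × √(2/n): 0.085 at n = 70 (100 less the assumed 30% loss) and 0.071 at n = 100. For a fully treated against a fully untreated group, z = 1.6 to 3.1 at 70 and 1.9 to 3.7 at 100. If the treated shares differ by only half, z at 100 per group halves to about 1.0 to 1.9.

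**The case against.** The strongest reply is that this leans on an omission from a condensed article. Table 2 is captioned as routine clinical investigations, nothing says it is the whole case report form, and Data management, storage and security describes a wider database. A treatment field or a sensitivity analysis may exist in the full protocol or SAP. That is fair for the missing item. It does not reach the sampling window or the predictor rule, which the article states and which create the exposure.

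Several stronger readings are tempting, and the documents do not support them:

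- **That signatures will measure treatment.** Only *can* is supportable, because treated shares and delays are not given.
- **That treatment can never be separated afterwards.** Days in hospital are recorded and charts may recover the rest. Hematocrit and hemoglobin are also in Table 2, though plasma leakage and dilution both move hematocrit, so it is a poor proxy.
- **That transfused donor material will appear as a marker.** This needs transfusion before deterioration, which nothing in the article shows. Early fluids are the more plausible route.
- **That the artefact would replicate in India.** One sampling window is stated for both cohorts, so it could, but care patterns at the sites are not described.
- **That the dilution figures are typical.** They assume fully treated against fully untreated groups. Their low ends, 1.6 and 1.9, do not reach even unadjusted 5% significance, and the plan corrects for multiplicity. A uniform shift also favours no particular protein for a panel of 5 to 10.

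Nor does it follow that the main analysis should adjust for treatment. Treatment tracks emerging severity, so adjustment could remove real prognostic signal and would extrapolate where groups hardly overlap.

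**Conclusion.** The point holds as a possible bias of unknown size. The stated window and predictor rule admit samples taken after treatment has begun, the article itself says treatment alters the profiles, and the printed questionnaire does not capture it. Contrasts of mainly inpatient groups with outpatients are most exposed. Dengue with warning signs against severe dengue is less so if both groups are mainly inpatients, although treatment intensity may still differ.

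The bias runs from negligible to dominant across the assumed range, according to the treatment effect and the difference in treated share. The conclusion rests on one assumption beyond the text: that care before the draw rises with eventual severity. The acknowledged limitation on timing from symptom onset does not cover it, because two patients on the same day of illness can differ in care received. It is worth correcting now. By June 2026, 170 of the planned 400 Guatemala participants (4 × 100, controls included) had been enrolled, and the 600 planned for India (4 × 150) start in July 2026.

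**What to change.** 1. Add to the Table 2 questionnaire whether intravenous fluids, blood products or other inpatient drug treatment were given before the draw, with start time. Complete this from charts, where possible, for patients already enrolled. If the full case report form already holds these items, say so.
2. Take the research sample with the admission blood draw where feasible, without changing or delaying care, and record hours since admission.
3. Keep the main biomarker analysis as planned. Pre-specify a sensitivity analysis restricted to samples drawn before treatment or, where treatment is unknown, on the day of admission, using the days-in-hospital item already collected. Day-of-admission samples may still follow some treatment, so report the two sources separately. Add an analysis within inpatients only.
4. For the panel candidates, report effect sizes with confidence intervals from these analyses next to the main results, and flag candidates whose effect shrinks materially. Agreement in direction alone is too weak a test, since a null marker passes about half the time.

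The cost is a few form items, a chart look-back and two further analyses. The restricted estimates will be less precise, so a wide interval should be read as lack of information and not as reassurance.

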**Disease symptoms at the time of sampling**	
Duration of symptoms onset at sample collection	In days
Duration of hospitalization at sample collection	In days
Fever	Yes/No
Body pain	Yes/No
Joint pain (arthralgia)	Yes/No
Rash	Yes/No
Nausea/vomiting	Yes/No
Night sweats	Yes/No
Retro-orbital pain	Yes/No
Abdominal pain	Yes/No
Headache	Yes/No
Chills/ rigor	Yes/No
Burning micturition	Yes/No
Dizziness	Yes/No
**Diet/Lifestyle**	
Vegetarian	Yes/No
Meat eater	Yes/No
Alcohol	Yes/No
Smoking	Yes/No
**Clinical biochemistry**	
Hemoglobin	g/dL
White Blood Cells	(value)/µL
Differential Lymphocyte Count (eosinophils, neutrophils, lymphocytes)	(value)/ µL
Platelets	(value)/ µL
Hematocrit	%
Procalcitonin	mcg/L
Total bilirubin	mg/dL
Aspartate Transaminase	IU/L
Alanine Transaminase	IU/L
Alkaline Phosphatase	U/L
Urea	mg/dL
Creatinine	mg/dL
Partial Thromboplastin Time	seconds
Activated Partial Thromboplastin Time	seconds
Serum Lactate Dehydrogenase	U/L
Lactate Oxidase (Arterial Blood Gas)	mg/dL
Creatinine Phosphokinase	U/L
Troponin T	ng/mL
N-Terminal Pro- B-Type Natriuretic Protein	pg/mL

#### Multi-omics studies and biomarker identification

We will perform RNA sequencing (RNA-seq) of the blood cells [10], proteomics by Olink^®^ Reveal, and metabolomics using liquid chromatography-mass spectrometry (LC-MS/MS) in the samples collected from Guatemala [11, 12]. Due to different numbers of analytes, i.e., genes from RNA-seq (n = ~ 20000), protein (n = ~ 1034) and metabolites (n = ~ 1200), we will first identify biomarkers associated with disease severity in each omics dataset using Random Forest for feature selection, and Bayesian belief network (BBN) based structural causal modelling to infer putative causal relationships [12]. To further refine the biomarkers, we will perform integrative analysis using the Consensus Association (CA) analysis and gene/protein/metabolite cooperation networks by integrating the transcriptomics, proteomics and metabolomics analysis to identify a robust mechanism-informed protein biomarker panel for clinical translation [9]. Additionally, a high-throughput analysis of total plasma, IgG, and/or IgM N-glycome [13, 14] from the available patient cohorts will be performed to evaluate glycosylation as a biomarker of disease severity. For Indian samples we will perform RNA-seq of the blood cells and proteomics by Olink^®^ Reveal.

### Single cell RNA sequencing (scRNA-seq)

In a subset of samples (~ 20–25%) scRNA-seq will be performed using two different platforms to generate cross-validated data and to establish a scalable framework for future dengue infection studies as well as future pandemic preparedness. In the Guatemala cohort, instrument-free Parse Biosciences Evercode platform will be used for large-scale sample multiplexing and transcriptomic profiling through split-pool combinatorial barcoding, while minimizing batch effects and improving cohort-level comparability. In the Indian cohort, microfluidics-based 10x Genomics Chromium scRNA-seq protocol will be used to generate high-resolution transcriptomic profiles and resolve rare or functionally distinct cell populations. Running both in parallel will allow us to benchmark performance on matched infectious diseases questions, assess cross-platform results, and establish reproducible and scalable workflows that can be rapidly deployed in future outbreak responses. Following sequencing, reads will be processed using platform-specific pipelines, followed by harmonized quality control, normalization, dimensionality reduction, clustering, and cell-type annotation. Differential gene expression, pathway enrichment, trajectory analysis, regulatory network analysis and cell–cell communication analyses will be applied across both cohorts to identify disease-associated cellular states, regulatory programs, and intercellular signalling networks.

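### With one single-cell platform per country and no common samples described, the plan can show cross-cohort replication but cannot benchmark the platforms

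*Protocol article*

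**What the plan says.** The single-cell section of the protocol article gives the purpose of the sub-study as follows: "scRNA-seq will be performed using two different platforms to generate cross-validated data". The extent is a fraction of the collection: "In a subset of samples (~ 20–25%) scRNA-seq will be performed". The allocation is by country: "In the Guatemala cohort, instrument-free Parse Biosciences Evercode platform will be used", and "In the Indian cohort, microfluidics-based 10x Genomics Chromium scRNA-seq protocol will be used". The section then says what this will deliver: "Running both in parallel will allow us to benchmark performance on matched infectious diseases questions, assess cross-platform results". On processing it says that "reads will be processed using platform-specific pipelines, followed by harmonized quality control" and further common steps. Differential expression, trajectory and cell-communication analyses are then to be applied in both cohorts.

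The section mentions no specimen, donor or reference material to be run on both platforms. The matching it claims is on the disease questions, not on samples or donors.

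The Study procedures section lists blood material by country. For Guatemala, "whole blood is collected in Tempus™ tube for transcriptomics and in Cytodelics medium for flow cytometry", plus EDTA plasma and serum. For India there are Tempus tubes, and blood is also drawn "in BD Vacutainer CPT™ Cell Preparation Tubes for plasma separation and PBMC isolation". Neither section says which specimen feeds the single-cell work in either country.

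**The concern.** A platform benchmark needs the two platforms to be compared on something held constant. Here everything else changes along with the platform:

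- the country and its patients;
- the calendar period: the Study status section gives a start in January 2025 for Guatemala and July 2026 for India;
- the read-processing pipeline.

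The limitations paragraph of the Discussion already expects population differences between the two settings, but it does not list platform among the reasons why signatures may fail to overlap.

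What is at stake is the conclusion that may be drawn. If a cell state appears in one cohort and not in the other, the cause could be the platform, the population, or possibly the cell source, and the data cannot say which. A report that presents the difference as platform performance, or as biology, would go beyond the design. The single-cell data also feed the patient-based metabolic model, so the question of what a discordant result means does not stay inside this sub-study.

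**Working it through.** The plan gives no sample size or precision for the platform comparison, so there is no figure to reproduce. The check is one of estimability.

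**Inputs.** Four groups in each cohort (three severity categories and healthy controls), with 100 per group in Guatemala and 150 per group in India (Study cohorts; Recruitment of controls). Guatemala uses Parse only and India 10x only (single-cell section).

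**Size of the subset.** Assume one sample per participant and the same fraction in each cohort and group.

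- Guatemala: 4 × 100 = 400; 20–25% is 80–100, or 20–25 per group.
- India: 4 × 150 = 600; 20–25% is 120–150, or 30–37.5 per group.
- Samples described as run on both platforms: none.

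These counts are only indicative. The article speaks of samples, and hospitalized patients give two.

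**Model.** Write the mean of any single-cell measure as an intercept μ, a country effect C (India), a platform effect P (10x), severity effects S, severity-by-country effects SC and severity-by-platform effects SP. The parameters number 1 + 1 + 1 + 3 + 3 + 3 = 12.

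**Planned layout.** Only two country–platform combinations exist, each with four groups, so there are 2 × 4 = 8 cell means. The columns for country and platform are identical.

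- Intercept, country and platform together: rank 2 of 3.
- Full model: rank 8 of 12.

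In the healthy controls, India minus Guatemala equals C + P. Only the sum is identified. For severe dengue against healthy controls:

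- Guatemala on Parse: S. Estimable.
- India on 10x: S + SC + SP. Estimable.
- Difference between the two: SC + SP. Only the sum is identified.

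So the contrasts within each cohort can be estimated and set side by side, but a discrepancy between them cannot be divided into a population part and a platform part. Adding samples repeats the same eight rows and leaves the rank at 8. Harmonized quality control and annotation do not add the missing combination either, and an adjustment that removes the difference between platforms also removes the difference between countries.

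**With a bridge.** If some samples from one country are run on both platforms across the four groups, there are 3 × 4 = 12 cell means and the rank is 12 of 12. P and SP become estimable. A fully crossed layout also gives 12 of 12. The one-country bridge assumes that the platform effect is the same in the other country.

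**The case against.** The strongest reply is that the sentence claims matching on questions and also aims at reproducible, scalable workflows. Describing how each workflow performs on the same disease needs no split samples. Each cohort has its own healthy controls and all severity groups, so a severity signal found in both has survived a change of country and of platform, which is a fair sense of cross-validated. This stands. A reader might infer that no cross-validated finding is possible, or that results should be reported within cohort only. The documents do not support that, because the within-cohort contrasts are estimable and comparing them is legitimate. The reply does not rescue the head-to-head claim, since benchmarking and cross-platform assessment are stated outcomes.

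A reader might also infer that the two countries use different starting material. PBMC isolation is listed for India only, and the Guatemalan Cytodelics blood is assigned to flow cytometry. But the single-cell specimen is named for neither country, and an article may condense its tube list. The material may differ; it is not shown to differ.

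Nor does the article say that no sample will ever be run on both platforms; it describes none. The in vitro infection work also includes single-cell sequencing but is not said to use both platforms, so as written it supplies no bridge.

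Finally, the aim is ancillary. Single-cell sequencing appears in no objective or endpoint, and the targeted protein panel does not depend on a platform benchmark. This limits the weight of the point, not its correctness.

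**Conclusion.** The point holds for the benchmark and for cross-platform validation. As described, platform is completely aliased with country, population, recruitment start and read pipeline. The planned layout identifies 8 of 12 parameters, and the platform and severity-by-platform effects are not among the estimable quantities at any sample size. What remains valid is replication: agreement of the within-cohort severity contrasts supports a finding over country and platform jointly. Disagreement has no assignable cause.

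This rests on the article being complete on one matter, namely that no common samples are planned. If a fuller protocol provides for them, the article should say so and the point falls. Different starting material would be a further confounder, but the text leaves this open and the conclusion does not need it. The matter is worth correcting because it changes what may be concluded. It does not touch the primary endpoints as written.

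**What to change.** **Preferred, wording only.** In the single-cell section, state the aim as cross-cohort replication of severity contrasts estimated within each cohort. Remove the benchmarking and cross-platform validation claims. Add that discordant findings cannot be attributed to platform or to population. In Study procedures, name the specimen that feeds single-cell sequencing in each country. The cost is an edit to the text.

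**If the benchmark is to be kept.** Within the planned 20–25% subset, run split aliquots of the same cells on both platforms for a small set of participants spread over the severity groups. Indian PBMC are an obvious source, because they are already isolated and recruitment there starts only in July 2026. Set the number of pairs by a stated precision target for the platform difference; the documents give no basis for a particular number. Base platform claims on these pairs only, and state the assumption that the platform effect carries over to Guatemala and to whatever material is used there. The cost is set-up of the second platform or transfer of samples, and slightly fewer distinct participants if the subset size is held fixed. No additional sampling visit should be needed if the aliquots come from cells already isolated.
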